## Methods

### Trial design

The study will involve a pragmatic, randomised, controlled parallel-arm pilot trial of a re-implementation intervention. We have elected to randomise at the level of the clinician, as our primary focus is understanding the potential effectiveness of the re-implementation package. Also, while context exerts a significant influence on implementation [31], individual behaviour change remains at the core of implementation success, even where there is significant influence from organisational factors [32]. In fact, individual factors such as attitudes may be more predictive of implementation than organisational factors, and individual-level barriers may be more amenable to intervention [32]. Also, we are interested in understanding where (i.e. which clinical settings) clinicians choose to adopt PCIT as a result of the intervention, in order to inform the design of the future trial.

### Participants

#### Inclusion criteria

Clinicians must have completed a recognised 40-h initial training in PCIT no earlier than 2010 (when PCIT was introduced to Aotearoa/New Zealand) and be registered to practise in Aotearoa/New Zealand at the time of participation in the trial. Having been eligible for the PCIT initial training implies that included clinicians will be allied health and medical clinicians with a Master’s degree or equivalent (i.e. psychologists, psychiatrists, social workers, psychotherapists, occupational therapists and nurses). Eligible clinicians are not required to be employed in a clinical role and may be in an administrative or managerial role, as it is possible that they may elect to adopt PCIT in a part-time private practice context. Where the clinician is already seeing a full caseload of PCIT clients (our preliminary research suggests this is unlikely), they will remain eligible for inclusion as we are interested in whether the provision of additional supports might influence the nature and quality of implementation. For example, the PCIT treatment protocol recommends the use of a time-out room in the Parent-Directed Interaction phase, and clinicians have indicated that this requirement can be problematic, which at times results in this phase being omitted or adapted [14].

#### Exclusion criteria

Clinicians who are based outside of the Tāmaki Makaurau/Auckland region will be excluded from this pilot trial, due to resource constraints. The mobile co-worker/consultant will be Tāmaki Makaurau/Auckland-based in the pilot trial.

#### Setting and proposed recruitment

Approximately 135 clinicians have received the 40-h initial PCIT training in Aotearoa/New Zealand since it was introduced in 2010. Participants will be recruited from a group of approximately 70 clinicians who are located in Tāmaki Makaurau/Auckland—Aotearoa/New Zealand’s largest city. The authors have an existing database of eligible clinicians, compiled for an earlier research project [14]. We will use the cultural practices of whanaungatanga to obtain details for those Māori clinicians who were unable to be contacted in the earlier study. Eligible PCIT-trained clinicians will then be approached via email, with a flyer inviting their attendance at a 1-h virtual information session. A second reminder email will be sent 2 weeks after the first approach. If an email address is unavailable, the first author will search publicly available information online and eligible clinicians will be approached by phone if necessary. If the clinician identifies as Māori, this phone call will be made by a Māori research team member to support culturally responsive practice. The flyer and Participant Information Sheet will also be distributed by Whāraurau—a government-funded child and adolescent workforce development agency—to those clinicians who received training in PCIT through funding from the Ministry of Health.

At the information session, clinicians will be provided with information about what the trial will involve, the risks and benefits of participation, and will have the opportunity to ask questions. They will be asked to submit an expression of interest in receiving further information, confirming their details via a very brief online Qualtrics survey at the end of the session. If unavailable for the information session, clinicians can also submit an expression of interest independently. Those clinicians who choose not to express interest in proceeding to the trial will be asked (via the Qualtrics survey) for a brief reason why they do not want to, or are not able to, proceed. This information will be used to inform recruitment processes for the future trial including specific tikanga Māori practices.

Clinicians who express interest will be emailed a full Participant Information Sheet (PIS) and consent form. Those who consent to participate will be invited to a two-day PCIT refresher training in Tāmaki Makaurau/Auckland (refer below).

#### Randomisation and blinding strategies

All participants will have been recruited and will have participated in the two refresher training days (refer ‘Study Treatments’, below) prior to random allocation to intervention and control groups. Allocation to groups will occur at the end of the second day of refresher training. A random allocation sequence will have been generated by the study statistician (using a simple 1:1 randomisation with no restrictions), who will contact participants via email with their group allocation. Participants will be asked not to share the email or reveal or discuss the condition to which they have been allocated. We will undertake a test of blinding at the end of the intervention (i.e. will ask participants which condition they believed themselves to have been allocated) in order to determine whether blinding is feasible in a future trial.

The first author will be delivering some of the re-implementation supports and will therefore be unable to be blinded. The remainder of the research team, particularly outcome assessors, will be blinded.

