What	**Materials** • Participating clinicians will have access to a Dropbox folder of PCIT-related resources, including research articles, slides from relevant presentations, handouts and worksheets. These have been produced by a number of different PCIT researchers and clinicians • Clinicians will be provided with a toy package of approximately $NZD700 value, containing toys selected by two senior PCIT clinicians (Māori and non- Māori) as being suitable for use in PCIT • Two robust Voyager Compact travel bed tents from Safespaces UK (www.safespaces.co.uk) will be available for clinicians to book, to use as portable time-out spaces for children. Setup support will be provided to clinicians • Audio-visual equipment will include a ‘baby monitor’ kit, to allow remote camera viewing and audio from the adjacent room, by a clinician located in a separate space to the parent and child. A basic mobile phone and earpiece worn by the parent will allow clinicians to discretely provide coaching out of the child’s hearing **Procedures** • Refresher training content will be compiled and delivered by two senior PCIT-trained clinicians (Māori and non-Māori), one of whom is a Within-Agency Trainer for PCIT. It will include pre-existing video content from the UC Davis PCIT web course, and the Auburn University PCIT continuing education videos. The two trainers will also facilitate discussions and problem-solving sessions relating to how to deliver PCIT in a culturally responsive way, navigating client or colleague concerns relating to the use of time-out, and other topics that have been identified in our earlier research as impeding or influencing implementation. These discussions will be informed by the trainers’ own research and clinical experience
Who provided	The refresher training will be delivered by two PCIT-trained clinical psychologists, one of whom is Māori, and one of whom is a PCIT International accredited Within-Agency Trainer. The co-worker is an accredited PCIT provider, a Māori clinical psychologist. The weekly PCIT consultation groups will be facilitated by the first author, with support from the co-worker, who will also attend

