### Statistical considerations

#### Sample size and justification

As this is a feasibility study, sample size calculations are not required, and a formal power calculation is not appropriate, given that the primary outcome for this pilot is feasibility [38]. Instead, sample sizes for feasibility studies should be based on pragmatic considerations [39]. However, for the RCT, it is envisaged that the primary outcome will be *adoption*: clinician self-report of the number of unique families to whom PCIT was delivered in the most recent representative 1-week period at 6 months post-randomisation, compared to baseline. These data will be collected.

Relevant pragmatic considerations included the size of the group of PCIT-trained clinicians thought to be practicing in the Tāmaki Makaurau/Auckland region, excluding the research team (approximately 70). Also, the budget for the research project will only support limited co-worker hours, and the purchase of limited time-out pop-up cubicles and limited audio-visual equipment and toy packages. Given these practical constraints, we hope to recruit 10 participants per condition or 20 overall. We are interested in evaluating whether the proposed recruitment methods will be effective in a future, larger trial. While we will aim to recruit this number, our ability to do so will provide valuable data around our ability to recruit sufficient participants for a fully powered trial using the described methods.

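### Unrestricted 1:1 randomisation of about 20 clinicians does not ensure the resource-driven target of 10 per condition, although everyone is enrolled before a single allocation step

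*Protocol article*

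**What the plan says.** The section on randomisation and blinding strategies has the study statistician generate the sequence "using a simple 1:1 randomisation with no restrictions". Recruitment and both refresher days are complete by then: "Allocation to groups will occur at the end of the second day of refresher training".

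The section on sample size and justification makes no power calculation. It sets the target from pragmatic limits, saying that "the budget for the research project will only support limited co-worker hours, and the purchase of limited time-out pop-up cubicles", and adding "limited audio-visual equipment and toy packages". It then concludes: "Given these practical constraints, we hope to recruit 10 participants per condition or 20 overall".

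The Intervention section and Table 1 show how these resources relate to arm size. In Table 1, "Clinicians will be provided with a toy package of approximately $NZD700 value"; the packs are listed as an intervention component and each clinician holds their own. Two time-out tents, the audio-visual equipment and the co-worker are shared through a booking system, and co-worker contacts per clinician have no upper limit.

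The progression criteria ask for 20 or more enrolled clinicians and give no maximum. The protocol states no cap on the intervention arm and no plan for an unequal split.

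**The concern.** The target is stated per condition, and the reason given is the supply of items that only the intervention arm receives. The size of that arm is therefore the number the resource argument depends on. The allocation method leaves it to chance: each clinician is in effect assigned by a separate coin toss, and the explicit absence of restrictions rules out reading 1:1 as a guaranteed equal split.

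At stake is mainly logistics. A larger intervention arm needs more toy packs and puts more clinicians in line for two tents and one co-worker. Bookings serve as the proxy for acceptability of those items, so scarcity could lower them for reasons unrelated to acceptability. A smaller intervention arm leaves fewer clinicians from whom to learn about the package.

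**Working it through.** **Inputs.** N = 20 with 10 per condition (sample size section); independent allocation with probability 0.5 (randomisation section); toy pack about NZD 700 each, one per intervention clinician (Table 1 and the text below it). The target is pragmatic, so there is no power calculation to reproduce. The plan's own arithmetic agrees: 2 × 10 = 20, and the expected arm size is 20 × 0.5 = 10.

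**Arm size.** Let X be the number in the intervention arm. X ~ Binomial(20, 0.5), with P(X = x) = C(20, x)/2^20 and SD = √(20 × 0.5 × 0.5) = 2.24.

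- Exactly 10:10: C(20, 10)/2^20 = 184,756/1,048,576 = 17.6%, so the target split is missed with probability 82.4%.
- More than 10 in the intervention arm: (1 − 0.1762)/2 = 41.2%. Of this, 16.0 points are an 11:9 split (167,960/1,048,576).
- 12 or more in the intervention arm: 25.2%; 13 or more: 13.2%; 14 or more: 5.8%.
- Imbalance in either direction, by doubling: 12:8 or worse 50.3%; 13:7 or worse 26.3%; 14:6 or worse 11.5%.

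**Other enrolment totals.** At N = 18, P(X > 10) = 24.0%, where an equal split would give 9. Above 20 the probability rises (58.4% at N = 22, 72.9% at N = 24), but an equal split would itself give 11 or 12, so those figures reflect enrolment as well as the allocation method.

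**Cost of toy packs.** 10 × 700 = NZD 7,000; 13 × 700 = NZD 9,100. If 10 were a hard ceiling (an assumption), the expected excess at N = 20 is half the mean absolute deviation: ½ × 10 × 0.1762 = 0.88 packs, or about NZD 620. If the ceiling were 12, the chance of exceeding it would be 13.2% instead of 41.2%.

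**Precision of the comparison of means.** Relative efficiency is 4·n₁·n₂/N², and the standard error grows by the factor 1/√efficiency.

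| Split | Efficiency | Increase in SE |
|---|---|---|
| 12:8 | 4 × 96/400 = 0.96 | 2.1% |
| 13:7 | 4 × 91/400 = 0.91 | 4.8% |
| 14:6 | 4 × 84/400 = 0.84 | 9.1% |

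**With equal allocation.** A random permutation that assigns 10 of 20 gives 10:10 with probability 1, and P(X > 10) falls from 41.2% to 0.

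**Baseline PCIT use (illustration only).** The 2021 survey cited in the Background gives a median of 0 clients per week (IQR 0 to 1), so roughly a quarter or more may have a current client. Assuming 5 such clinicians among 20, simple randomisation splits them 4:1 or worse with probability 2 × (5 + 1)/32 = 37.5%. Assuming 8, a 6:2 split or worse has probability 2 × (28 + 8 + 1)/256 = 28.9%.

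**The case against.** The best defence is that 10 per condition is a hope, not a specification, and is exactly what simple 1:1 allocation gives on average. The recruitment criterion has no upper limit, so 10 per arm is not treated as a ceiling. This stands: the scheme does not ensure the number, but it does not contradict it either.

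A reader might infer that an intervention arm above 10 would break the budget. The protocol does not support that. It calls the resources limited and gives no figure. Only the toy packs grow one-for-one with arm size; tents, audio-visual equipment and co-worker time are shared, and their load depends on uptake as well as headcount. A good part of the 41.2% is a single extra clinician.

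A reader might also infer that unequal arms undermine the pilot's results. They do not. The two primary outcomes (numbers enrolling and completing) and the three progression criteria are counted over the whole trial. Uptake of equipment and co-worker is measured in the intervention arm alone, so a larger arm gives more information on it. The pooled variance has 20 − 2 = 18 degrees of freedom whatever the split; only a single-arm SD suffers in the smaller arm. The t test on adoption is described as exploratory, and the precision loss is small.

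On baseline imbalance, the statistical methods section openly says that differences will be noted and not adjusted for. No passage says that baseline use predicts adoption at 6 months. Stratification is therefore a matter of choice.

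What the defence does not supply is a reason to prefer the unrestricted scheme. The protocol gives none, and the usual one, preventing prediction of the next assignment, has little force when everyone is allocated at once after enrolment closes.

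**Conclusion.** The point holds as a mismatch between two sections: the sample size section derives a per-condition number from limited resources, and the randomisation section uses a method that misses that split 82.4% of the time at N = 20 and puts more than 10 clinicians in the intervention arm 41.2% of the time. These figures assume 20 enrolled clinicians and independent allocation at probability 0.5. Any statement about the budget rests on the further assumption that 10 is a ceiling, which the protocol does not say.

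This is an inexpensive improvement to logistics and arm size. It is not a defect in validity: simple randomisation is unbiased, and the pilot's feasibility conclusions would stand under it.

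**What to change.** Replace the simple scheme by a random permutation of the final enrolled list that assigns half to each arm, with arms differing by one if N is odd and the larger arm then chosen by a rule set in advance. Keep the allocation email at the end of day 2. The cost is one sentence in the protocol and a few lines of code; concealment is unaffected because nobody is enrolled after allocation begins.

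If enrolment exceeds 20, equal allocation still gives an intervention arm above 10. It would help to state how many intervention clinicians the resources can support and what happens beyond that.

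Optionally, stratify on baseline PCIT use (no families against one or more) from the day 1 survey, since the analysis will not adjust for baseline differences. Where both strata have odd size, the extra clinician in one should go to the opposite arm from the extra clinician in the other, with the direction chosen at random, so that the arms stay equal overall.

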### Outcomes and measures

Baseline data will be collected from all participants, via a Qualtrics survey prior to allocation being revealed. The re-implementation intervention will be available for a period of 6 months to the intervention group. Some aspects of the re-implementation intervention occur at one point in time (e.g. the refresher training) and others continue across the trial period (e.g. access to equipment and co-worker, consultation). All aspects of the intervention will be contained within a 6-month period and will cease at that point. Table 2 provides a summary of outcomes and measures.

**Table 2 Tab2:** Summary of outcomes, measures and time points

		**0**	**1**		**2**		**3**	
**Method**		**Pre-trial information session**	**Baseline (beginning of day 1 of refresher training)**		**Monthly throughout trial (begins 1-month post-randomisation)**		**End of trial (6 months post randomisation)**	
			**Control**	**Intervention**	**Control**	**Intervention**	**Control**	**Intervention**

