**Adoption**								
Study-specific Qualtrics questionnaire	Number of families provided with PCIT in past 1 week		X	X	X	X	X	X

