#### Secondary outcomes

Acceptability of trial processes to participants will be measured by a study-specific survey following the pre-trial information session and at the end of the trial. Those who choose *not* to enrol in the trial following the information session will also be asked to complete the study-specific survey as to their reasons for non-participation, and a frequency count of responses to these multiple-choice items will be undertaken.

Clinician self-reported Capability, Opportunity and Motivation to use PCIT (drawn from COM-B theory; [23]) will be measured by Likert scale items within a monthly self-report survey, developed for the purposes of this trial and delivered via Qualtrics.

Acceptability of the monthly surveys as a data collection method, and the timing and frequency of these, will be measured by response rates. Also, a post-trial semi-structured phone interview will incorporate Likert scales and seek participants’ ratings of the acceptability of the monthly surveys as a data collection method.

Acceptability of each aspect of the re-implementation intervention will be assessed by participant uptake of the components. As an online booking system will be used to coordinate the loan of (1) the audio-visual equipment, (2) the time-out cubicle and (3) the mobile co-worker, a frequency count of weekly bookings will be used as a proxy measure for the acceptability of these items.

Also, in a post-trial semi-structured phone interview, participating clinicians will be asked to rate the acceptability of the components of the re-implementation package on a series of Likert scales. Acceptability of group consultation sessions will be assessed by participant attendance rates, measured by an audit of session attendance registers.

Clinician adoption of PCIT will be assessed by clinician self-report of the number of unique families to whom PCIT was delivered in the most recent representative 1-week period at 6 months post-randomisation and compared to baseline (via the study-specific monthly survey). Given that PCIT sessions are typically held weekly, this is expected to provide a valid measure of clinician PCIT adoption.

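### Participants are told their arm by email, so asking them which arm they believe they were in cannot show whether blinding is feasible, and the stated extent of blinding is too broad

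*Protocol article*

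**What the plan says.** Four statements matter here.

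- **Participants learn their arm.** Randomisation and blinding strategies has the statistician generate the sequence, "who will contact participants via email with their group allocation". It continues: "Participants will be asked not to share the email or reveal or discuss the condition to which they have been allocated". Outcomes and measures places the baseline survey before this moment: "via a Qualtrics survey prior to allocation being revealed".
- **Participants are then tested for blinding.** At the end of the intervention the team "will ask participants which condition they believed themselves to have been allocated", "in order to determine whether blinding is feasible in a future trial". Table 2 schedules this at end of trial in both arms.
- **Staff are said to be blind.** The first author is declared unblinded because of delivering some of the supports. For the others: "The remainder of the research team, particularly outcome assessors, will be blinded".
- **Adoption is self-reported, with two wordings for the week.** Secondary outcomes defines it as the clinician's own report of the "number of unique families to whom PCIT was delivered in the most recent representative 1-week period at 6 months post-randomisation", and Sample size and justification repeats that wording for the envisaged primary outcome of the definitive trial. The adoption row of Table 2, used at baseline, monthly and at end of trial, reads "Number of families provided with PCIT in past 1 week".

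**The concern.** A blinding test is informative only if its result could have gone either way. Here respondents are asked about something they were told six months earlier and have seen confirmed by what they did or did not receive. The protocol nevertheless gives the result a purpose, a conclusion about blinding in the next trial, and that conclusion would rest on a question unable to support it. The useful question, whether staff stayed blind, is not asked.

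The general statement about blinded staff has a related weakness. It makes one exception, although the statistician necessarily knows the allocations. Nor can it extend to adoption, because the person who assesses that outcome is the participant.

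The reference week matters because the variability of adoption at the end of the intervention is to feed the sample size of the definitive trial (Study aims; Statistical methods). A fixed past week and a most recent typical week are different measurements. They can differ in level and in variance, and the second needs a judgement from a respondent who, after baseline, knows the arm.

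**Working it through.** No figure in the protocol is in dispute, so there is none to reproduce. The check sets the statements side by side and adds one illustration.

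**Step 1. Do participants know their arm?** The email gives the allocation, and the request for confidentiality presupposes that the recipient knows it. Outcomes and measures speaks of allocation being revealed. Setting and proposed recruitment describes an information session explaining the trial beforehand. The Intervention section and Table 1 give one arm only a toy package of about NZD 700, bookable audio-visual equipment and time-out tents, and a co-worker. Participants therefore know.

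**Step 2. What can the participant question show?** Inputs: 20 participants (Sample size and justification); 1:1 allocation, so the chance of a correct guess is 0.5 under true blinding; no answers of don't know (assumption). Let X ~ Binomial(20, p) be the number of correct answers.

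Under p = 0.5, 20 × 0.5 = 10 correct answers are expected. P(X ≥ 14) = 0.058 and P(X ≥ 15) = 0.021, so 15 is the smallest count with a one-sided tail below 0.05.

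| Probability of a correct answer | P(X ≥ 15) | Bang index per arm, 2p − 1 |
|---|---|---|
| 0.5 (true blinding) | 0.021 | 0 |
| 0.9 (assumed recall or reporting) | 0.989 | 0.8 |
| 0.95 (assumed) | 0.9997 | 0.9 |
| 1.0 (all report what they were told) | 1.00 | 1.0 |

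Only the lower three rows are realistic after the email. The result would be declared unblinded almost regardless of how the trial is run.

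**Step 3. Whom does the statement on staff blinding cover?**

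- Statistician: generates the sequence and sends the allocations, so is not blind. The text does not list this exception.
- Adoption: reported by the clinician through an online survey. The baseline report is made before the arm is known, the later ones after. No staff assessor comes between the clinician and the count.
- Audits of enrolment and completion logs, and withdrawal contacts made by someone other than the first author (Primary outcome; Other considerations): handled by staff, so blinding them can have a purpose.

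**Step 4. Is adoption one quantity?** Table 2 names the past week without qualification. Secondary outcomes and Sample size and justification name the most recent representative week. They agree when the past week was typical and differ when it was not, for example during leave. The protocol does not say which wording the survey carries.

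**The case against.** The strongest reply is that little depends on this. The primary outcomes are enrolment and completion, taken from log audits. The three progression criteria are recruitment, attrition and survey response, and blinding is not among them. On that view the harm is one uninformative survey question. This stands and limits the weight of the point. It does not rescue the question, which has a stated purpose that it cannot serve.

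It may also be said that the email could carry only a neutral group label. Its text is not shown, but the protocol refers to the condition allocated, and the arm-specific supports would reveal it in any case.

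On the reference week, Table 2 is a summary and its row may be shorthand for the definition given twice in the text. That is plausible. The qualifier representative also guards against atypical weeks, so removing it would be a trade-off and not a plain improvement. What remains is that one wording must be chosen.

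Several stronger readings are tempting, and the document does not support them:

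- That staff blinding is worthless. It can still protect log audits and participant contacts.
- That a biased effect estimate is carried into the definitive trial. Study aims and Statistical methods carry variability forward, and the latter warns that effect estimates are unstable.
- That clinicians in the intervention arm would pick a busier week. Nothing shows this, and the wording limits the choice to the most recent representative week.
- That the end-of-trial interviewer breaks the blind. The interviewer is not identified and could be the first author, already declared unblinded.
- That the protocol presents adoption as blinded. It calls it self-report; the difficulty is only that the statement on blinded staff is not limited accordingly.

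**Conclusion.** The point holds in a limited form. The participant question cannot inform whether blinding is feasible: once participants have been told their arm, the chance of at least 15 correct answers in 20 rises from 0.021 to about 0.99 or more. This assumes that at least 90% report the arm they were told and that nobody answers don't know. The statement that everyone but the first author is blinded is contradicted by the statistician's task and cannot cover adoption. The reference week has two wordings that should be reconciled, because the variance of this measure is to inform the definitive trial. How much the two wordings would change that variance cannot be worked out from the protocol.

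What is affected is a secondary deliverable of the pilot: what it teaches about blinding and about the future primary outcome. Enrolment, completion and the progression criteria are untouched.

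**What to change.** 1. State that participants are not blinded after allocation, that participant-reported outcomes, including adoption, are therefore unblinded, and that the allocating statistician is unblinded as well as the first author. Say which staff and which tasks are blinded.
2. Replace the participant question with one put, at end of trial and before they are unblinded, to each staff member meant to be blind: which arm do they think each participant was in? Report the counts by arm descriptively. With 20 guesses only marked unblinding would show, since even 14 of 20 correct has probability 0.058 by chance.
3. Use one definition of the reference week in Table 2, Secondary outcomes, Sample size and justification and the survey itself, at every time point. If the past week is chosen, atypical weeks such as leave will enter the count. If the representative week is kept, tell respondents how to identify it. Averaging several monthly counts could steady the estimate but would not remove any reporting bias, so it does not replace a single definition.

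The cost is changes to protocol and survey wording and one extra question to staff. No additional participants or visits are needed.
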